## Abstract

**Backgrounds:**

Postoperative urinary retention (POUR) is one of the most common complications after hemorrhoidectomy. The best treatment for POUR is prevention and should be involved in the whole perioperative period. Moxibustion has been used to treat urinary retention for thousands of years, and clinical studies have also proved its effects. We try to carry out a randomized, controlled, prospective study to observe whether prophylactic moxibustion could effectively reduce the incidence of POUR of hemorrhoidectomy in 24 h.

**Methods:**

This study is a single-center, evaluator-blinded, randomized, and controlled trial. Participants who meet the inclusion and exclusion criteria in this RCT will be randomly assigned to either the treatment group (moxibustion) or the control group (tamsulosin hydrochloride) in a 1:1 ratio according to a computer-generated randomization list. Both moxibustion and tamsulosin will be used 1, 10, and 24 h after operation, respectively. The outcomes of occurrence of POUR, time to first urination, catheterization rate, urinary tract infection, length of hospitalization, and adverse effects will be recorded.

**Discussion:**

The findings of the study will help to explore the preventive efficacy of prophylactic moxibustion against POUR of hemorrhoidectomy in 24 h.

**Trial Registration:**

CHiCTR, CHiCTR2000039350, registered 24 October, 2020, http://www.chictr.org.cn/showproj.aspx?proj = 63204.

## Background

The optimal treatment for circumferential mixed hemorrhoids is surgery (1, 2), and urinary retention is one of the most common complications after hemorrhoidectomy, with an incidence of 32.8% (3) or even higher. Mostly, postoperative urinary retention (POUR) is caused by anesthesia and analgesia, intravenous fluids, mental tension, and duration of surgery. POUR can easily cause urinary tract infections and secondary reflux nephropathy, which increases the suffering of patients and prolongs their recovery (4).

Catheterization is the main effective method for resolving POUR, but it may lead to urethral injury and stricture to increase the predisposition for urinary tract infections (UTIs). After the withdrawal of the catheter, the patients may also suffer from POUR, which could increase the cost of the hospitalization period. Therefore, the best treatment for POUR is prevention and should be involved in the whole perioperative period (5–7). The methods of controlling intraoperative intravenous fluid volume, taking a slow time to ambulate, and systemic opioids after the surgery are commonly used.

Several studies have demonstrated the benefit of prescribing alpha-blockers (prazosin (8), tamsulosin (9)) in preventing POUR (10), but these may cause many side effects such as headache and positional hypotension. In China, moxibustion is a commonly used method for urinary retention clinically. It is a traditional Chinese medicine therapy, and it plays an important role in the traditional medical systems of China against urinary incontinence, dysmenorrhea, knee osteoarthritis, soft tissue injury, heel pain, asthma, and urinary retention (11). Until now, there have been many studies on the effects of moxibustion on the human body (12–14), and clinical studies also proved the curative effect of moxibustion against POUR (15, 16). Mechanism studies have reported its thermal effects, radiation effects, and pharmacological actions to function as an analgesic, alleviating inflammation and enhancing immunity.

In our group, we tried to preliminarily perform prophylactic moxibustion on patients with prolapsed hemorrhoids right after surgery and found that it might be an effective way to reduce the incidence of POUR in 24 h. Therefore, we try to carry out a randomized controlled study with the following objectives: (1) to observe whether prophylactic moxibustion could effectively reduce the occurrence of POUR of severe prolapsed hemorrhoids in 24 h and (2) to provide evidence for promoting the application of moxibustion to prevent POUR. Tamsulosin will be used as an intervention in the control group because of its relatively more amenable side effects and greater patient satisfaction, as reported (17, 18).

## Methods

### Study Design

The study is a single-center, evaluator-blinded, randomized controlled trial (RCT). The protocol has been approved by the Ethics Committee of Changshu Hospital Affiliated to Nanjing University of Chinese Medicine, and the trial will be carried out in accordance with the Declaration of Helsinki. The protocol conforms to the Standard Protocol Recommendations for Interventional Trials (SPIRIT) 2013 Statement (19), and the results will be reported according to the CONSORT Statement extension for trials (20), the STandards for Reporting Interventions in Clinical Trials of Acupuncture (STRICTA) (28), and the STandards for Reporting Interventions in Clinical Trials of Moxibustion (STRICTOM). The clinical trial has been registered in CHiCTR (No.CHiCTR2000039350). The schedule of enrollment, interventions, and assessments is given in Table 1.

**Table 1 T1:** Schedule of enrollment, intervention, and assessments.

Time point	Enrollment	Treatment phase		
		1 h	10 h	24 h
**Enrollment**				
Eligibility screen	√			
Informed consent	√			
demographics	√			
History of disease	√			
Allocation	√			
Intervention				
Moxibustion		√	√	√
Tamsulosin		√	√	√
Assessments				
POUR incidence				√
Time to first urination				√
Catheterization rate				√
Incidence of UTI				√
Length of hospitalization				√
Adverse effects				√

### Participants

Participants will be recruited from inpatients of the Proctology Department of Changshu Hospital Affiliated to Nanjing University of Chinese Medicine, and they will be randomly assigned to either the treatment group or control group in a 1:1 ratio (Figure 1). The patients will be recruited from inpatients via posters in the department from March 01, 2021.

**Figure 1 F1:**
[figure not shown]
Flow diagram of the study.

### Inclusion Criteria

Patients will be included if they meet the following inclusion criteria:
(1)meet the diagnostic criteria for circumferential mixed hemorrhoids, with internal hemorrhoids grade III–IV;(2)aged from 18 to 70 years;(3)without obvious deformity of the anus before the operation; and(4)with written informed consent.

### Exclusion Criteria

Patients will be excluded if they present the following exclusion criteria:
(1)have undergone mixed hemorrhoids surgery or combined with other operations;(2)women in pregnancy, lactation, and menstruation;(3)with rectal cancer, rectal polyps, tuberculosis, Crohn's disease, and other anorectal diseases;(4)with glucose-6-phosphate dehydrogenase (G6PD) deficiency, inadequate conditions of butyrylcholinesterase enzyme, methemoglobinemia, and myasthenia gravis;(5)with severe respiratory, digestive, cerebrovascular disease, and obvious abnormal liver and kidney functions;(6)with urinary system diseases such as prostate hyperplasia, neurogenic bladder, urethral injury, urethral stricture; and(7)with ulcers, injuries, infections, scars, and allergies in the abdomen.

### Sample Size

The sample size estimate is based on a two-arm normal design. The ratio of the two groups is set as 1:1, and the significance level of the test is targeted at 0.05, with the power achieved to detect a difference set as 0.8. According to a previous literature report, the incidence of POUR after taking tamsulosin hydrochloride was 28.1% (21). In our preliminary experiment, the incidence of POUR after moxibustion therapy is 15%. Considering the dropout rate of no more than 20%, 180 cases will be required for each group.

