### Discontinue and Data Monitoring

Patients will be dropped if they are with the following conditions: (1) With severe adverse events (AEs); (2) Unwilling to continue the study protocol. The supervisor will make a decision to discontinue if more than 25% of the patients discontinue intervention due to AEs. Case report forms (CRFs) will be used in data collection to record demographics, assessments, and reasons for patient dropout. All CRFs will be stored in a locked cabinet. At the end of the study, the investigator will submit the CRFs to the data management committee, and the investigators cannot modify the data. The data monitoring committee is independently chaired by the Statistics Teaching and Research Office of Changshu Hospital Affiliated to Nanjing University of Chinese Medicine and claims no conflict of interest. All CRFs will be preserved for at least 5 years after publication, and access to the original data of readers and reviewers is available from the corresponding author on reasonable requests.

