### Statistical Methods

Full analysis set (FAS) and per-protocol set (PPS) will be both used for statistical analysis in this study. In FAS, for missing outcome data, multiple imputations will be used o. For continuous data, they will be represented as mean ± standard deviation and frequency or percentage for categorical data. Statistics will be analyzed with SPSS 22.0 (SPSS Inc., Chicago, IL). For primary outcomes, the chi-square test will be applied to analyze the POUR incidence. For secondary outcomes, the comparison of UTI incidence, AEs, and catheterization rate will be analyzed by the chi-square test; the independent-sample *t*-test or Mann–Whitney *U* test for intergroup comparison will be used for the time to first urination and the length of hospitalization after considering the normality and homogeneity. The dropout rates will be analyzed by the chi-square test, and the impact of the dropout rate will be further analyzed by comparing dropout reasons, characteristics of dropout cases between groups, and the results using intention-to-treat and per protocol. Statistical testing is two-sided, and *p* < 0.05 is considered statistically significant.

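### 180 per group falls slightly short of the 189 to 193 that the printed inputs need at 20% dropout; power at that ceiling is about 77 to 78%, not 80%

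*Protocol article*

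**What the plan says.** The Sample Size section of the protocol article gives all the inputs. On allocation it says "The ratio of the two groups is set as 1:1", on type I error "the significance level of the test is targeted at 0.05", and on power "with the power achieved to detect a difference set as 0.8". The assumed POUR incidence is 28.1% with tamsulosin, from a literature report, and 15% with moxibustion, from the group's own preliminary experiment. The section then concludes: "Considering the dropout rate of no more than 20%, 180 cases will be required for each group".

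It does not say whether the test in the calculation is one- or two-sided. Statistical Methods settles this for the analysis ("Statistical testing is two-sided, and" a 0.05 threshold) and names the chi-square test for POUR incidence. Neither section prints the number of evaluable patients before dropout or the formula used to inflate it.

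**The concern.** A dropout allowance should leave enough patients for the stated power when dropout reaches the rate allowed for. Here the reader is told that 180 per group covers losses of up to 20% and keeps 80% power. If the arithmetic does not support that, the protocol credits the design with a power it lacks at its own planning limit, and a null result on POUR would be read against a figure that is somewhat too high. This is not a matter of detail left out of a condensed article: the inputs and the result are both printed, and the result does not follow from the inputs.

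**Working it through.** **Inputs.** From Sample Size: p1 = 0.281, p2 = 0.15, difference 0.131, alpha 0.05, power 0.80, ratio 1:1, dropout up to 20%, 180 per group. From Statistical Methods: two-sided testing, chi-square test. Normal quantiles: 1.960 and 0.842.

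**Evaluable patients needed per group.**

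- Unpooled variance: n = (1.960 + 0.842)² × [0.281 × 0.719 + 0.15 × 0.85] / 0.131² = 7.849 × 0.3295 / 0.01716 = 150.7, so 151.
- Pooled variance under the null (mean rate 0.2155): n = [1.960 × √(2 × 0.2155 × 0.7845) + 0.842 × √0.3295]² / 0.131² = (1.960 × 0.5815 + 0.842 × 0.5741)² / 0.01716 = 153.5, so 154.
- Arcsine transformation: 151.4, so 152.

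**Trying to reproduce 180.**

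| Method (two-sided) | Evaluable n | n / 0.8 | n × 1.2 |
|---|---|---|---|
| Unpooled | 151 | 189 | 182 |
| Arcsine | 152 | 190 | 183 |
| Pooled | 154 | 193 | 185 |

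Dividing by 0.8 never gives 180 with the printed rates. One-sided testing does not explain it either: the same methods then need 119 to 121 evaluable patients, or 149 to 152 after division by 0.8. Multiplication by 1.2 comes close, and a rounded 150 × 1.2 is exactly 180.

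**What 180 delivers.** At 20% loss, 180 × 0.8 = 144 per group remain.

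- Unpooled: standard error √(0.3295 / 144) = 0.04784; 0.131 / 0.04784 − 1.960 = 0.778; power 78.2%.
- Pooled: null standard error √(2 × 0.2155 × 0.7845 / 144) = 0.04846; (0.131 − 1.960 × 0.04846) / 0.04784 = 0.753; power 77.4%.
- Exact enumeration of the uncorrected chi-square test: 78.1%.

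**Power by loss, starting from 180 per group.**

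| Loss | Evaluable per group | Power, pooled | Power, unpooled |
|---|---|---|---|
| 0% | 180 | 85.9% | 86.5% |
| 5% | 171 | 84.1% | 84.7% |
| 10% | 162 | 82.1% | 82.8% |
| 20% | 144 | 77.4% | 78.2% |

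The loss at which power falls to 80% is 1 − 154/180 = 14.4% (pooled) or 1 − 151/180 = 16.1% (unpooled).

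**Sensitivity to rounding of the pilot rate.** The moxibustion rate is printed as a whole percentage. If the unrounded value were 14.7%, the unpooled formula gives 143.1, so 144, and 144 / 0.8 = 180. At 14.6% the pooled formula gives 143.4, so 144, and again 180. Over 14.5% to 15.4%, correct division gives 174 to 203 (unpooled) or 178 to 207 (pooled).

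**The case against.** Several points weigh against making much of this.

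*The cause is not shown.* A reader might infer that the sponsor multiplied by 1.2 where division by 0.8 was needed. That is plausible, but the protocol prints neither the evaluable number nor the inflation step, and 151 × 1.2 or 154 × 1.2 does not give exactly 180. A pilot rate of about 14.6 to 14.7%, printed as 15% and correctly inflated, would also give 180. This stands as a limit on the diagnosis. It does not rescue the text, because it needs an input that the protocol does not state, and the printed figures still do not yield 180.

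*The 20% is a ceiling.* A reader might infer that the trial simply has 78% power. It does not: that figure applies only if loss reaches the ceiling and those patients contribute no primary outcome. The patients are inpatients and the outcome falls within 24 h, so actual loss may be well below 20%. This stands, and the conclusion is conditional on it. The allowance is nevertheless presented as covering 20%, and at 20% it does not.

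*Multiple imputation is planned for the full analysis set.* Imputing a missing binary primary outcome restores little information unless strong predictors are available, and the protocol names none. The per-protocol analysis loses these patients altogether.

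*The stopping rule might suggest that heavier loss is tolerated.* Discontinue and Data Monitoring says: "The supervisor will make a decision to discontinue if more than 25% of the patients discontinue intervention due to AEs". A reader might take this as accepting 25% loss for the power calculation. It does not support that. It concerns stopping the intervention because of adverse events, and a patient who stops the intervention can still have a 24 h outcome.

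*A continuity correction would widen the gap.* Statistical Methods names the chi-square test and mentions no correction, so the document gives no ground for judging the design by the corrected statistic.

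**Conclusion.** The sample size statement is wrong as written, by a small amount. On the printed rates, with a two-sided test at 0.05 and 80% power, a 20% allowance requires 189 to 193 per group: 9 to 13 more than the stated 180, or 378 to 386 in total against 360. At 20% loss the design has 77.4 to 78.2% power, a shortfall of 1.8 to 2.6 points.

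This rests on three assumptions: the printed 15% is taken at face value, the calculation is two-sided like the analysis, and lost patients supply no primary outcome. The documents do not establish how 180 was reached, and they do not support calling the trial underpowered whatever the actual loss.

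**What to change.** Restate the Sample Size paragraph so that its figures agree. It should say that the calculation is a two-sided comparison of two independent proportions at alpha 0.05, with 28.1% against 15%; that 180 per group gives about 78% power if 20% of patients have no primary outcome; and that power is at least 80% while no more than about 14% are lost. Print the evaluable number and the inflation step. If the pilot rate was not exactly 15%, print the value used and recompute the figures from it.

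No extra enrolment and no change to the analysis is needed. The cost is one amended paragraph and a slightly less favourable power statement, best made before results are read.

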### Randomization

Patients will be randomly divided into a treatment group (moxibustion) and a control group (tamsulosin hydrochloride) in a 1:1 ratio. The randomization sequence will be generated by an independent statistician not involved in the statistical analysis with SPSS 22.0 software. The random numbers will be placed in opaque, sealed envelopes and kept in a safe place until the study is complete.

### Blinding

All patients will be informed to be equally allocated to the treatment group and control group before enrollment. Blinding of moxibustion is quite difficult to achieve. The treatment will be performed by trained and experienced moxibustion members. Surgeons, moxibustion practitioners, and patients will not be blinded due to the limitation of treatment, while outcome assessors and statisticians will be blinded to treatment allocation.

### Interventions

The same operation (tissue selecting technique with a mega-window stapler combined with anal canal epithelial preservation operation), anesthesia, and intraoperative and postoperative management will be performed for patients in both groups. Subarachnoid anesthesia will be applied with 10 mg of Naropin at L3–4. The intraoperative fluid is 500 ml, and the postoperative fluid is 500 ml for anti-infection and hemostasis.

### Treatment Group

Moxibustion therapy will be used 1, 10, and 24 h after operation. Moxibustion members who have more than 1-year experience in mild moxibustion will be retrained for standard management of the study. The moxa rolls for moxibustion are produced by Nanyang Chinese Medicine Airong Co. Ltd., in 18 × 200 mm. Points of Qihai (CV 6), Zhongji (CV 5), Guanyuan (CV 4), and bilateral Sanyinjiao (SP 6) will be selected for moxibustion.

In the procedure of moxibustion, the patient takes the supine position with the abdominal skin exposed; the moxibustion members lit the moxa rolls and put them 2–3 cm above the five points for 20 min. When the patients cannot urinate with urgent micturition desire within 24 h after the operation, catheterization will be performed.

### Control Group

Tamsulosin hydrochloride [0.2 mg, Astellas Pharmaceutical Co., Ltd., China] will be given once to patients 1, 10, and 24 h after operation. When the patients could not urinate with urgent micturition desire within 24 h after the operation, catheterization will be performed (Table 1).

### Outcome Variables

#### Primary Outcomes

*POUR incidence*: POUR is deﬁned as any of the following (21, 22): (1) patient discomfort, a sensation of a full bladder, palpable, distended bladder, with a volume of urine 400 ml; (2) any estimated postvoid residual (PVR) volume of urine greater than or equal to 200 ml per bladder scan (21); and (3) need for catheterization in 24 h.

Patients are requested to freely report the sensation of a full bladder, palpable, distended bladder at any time after the operation. The occurrence of POUR in 24 h after the operation is recorded, and POUR incidence = the number of patients who meet the diagnosis of POUR/total number of included cases in each group.

#### Secondary Outcomes

(1)Time to first urination: the time from the end of the operation to the first urination.(2)Catheterization rate: the number of people who need catheterization in 24 h after operation in each group, catheterization rate = number of catheterization people/number of people included in each group.(3)Incidence of urinary tract infection (UTI): the occurrence of urinary tract infection during hospitalization, rate = number of infections/number of people included in each group.(4)Length of hospitalization: The average length of hospitalization of patients.(5)Adverse effects: Potential AEs may occur during the study. Patients may suffer from empyrosis, itching, allergy, dizziness with moxibustion and orthostatic hypotension, headache, dizziness, and vomiting with tamsulosin. The supervisor will manage the intervention, and any suspected AEs will be discussed with the principal investigator of the project team. If the patient shows any discomfort or changes in their condition, they are instructed to inform the investigators. The physician will provide the necessary treatment to alleviate any AEs.

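### The UTI outcome has no post-operative start or fixed end, counts infections instead of patients, and does not match Table 1; the likely bias is small and the repair is cheap

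*Protocol article*

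**What the plan says.** All references are to the protocol article.

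- **Secondary Outcomes, item 3 (UTI):** "the occurrence of urinary tract infection during hospitalization, rate = number of infections/number of people included in each group".
- **Secondary Outcomes, item 4:** "Length of hospitalization: The average length of hospitalization of patients". Statistical Methods plans a between-group test for it: a t-test or Mann–Whitney test "will be used for the time to first urination and the length of hospitalization after considering the normality and homogeneity".
- **Statistical Methods, for UTI:** "the comparison of UTI incidence, AEs, and catheterization rate will be analyzed by the chi-square test".
- **Comparable rates:** catheterization is "the number of people who need catheterization in 24 h after operation in each group". POUR is "the number of patients who meet the diagnosis of POUR/total number of included cases in each group", recorded over the same 24 h. Both count people over a fixed time.
- **Table 1:** the row "Incidence of UTI" has a single tick, which reads as the 24 h column.
- **Background:** POUR is said to lead to urinary infection, "which increases the suffering of patients and prolongs their recovery".

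**The concern.** Three features of the definition do not fit the planned comparison.

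1. **The end of the window is an outcome.** Observation for UTI stops at discharge, and time to discharge is compared between arms. If one arm goes home sooner, it is watched for less time, and a chi-square test on crude proportions makes no allowance for this. By the article's own reasoning, fewer POUR cases should mean quicker recovery, so a difference in stay favouring moxibustion is plausible. A lower UTI rate could then be read as a second benefit when part of it is shorter observation.
2. **The start is not tied to the operation.** Participants are recruited as inpatients, so the hospital stay begins before surgery and treatment.
3. **The numerator is events.** UTI is the only one of the three rates (POUR, catheterization, UTI) whose numerator is not people. A patient with two infections would contribute twice to a test that assumes one independent yes/no result per patient.

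In addition, a single assessment at 24 h and a count over the whole stay are different outcomes, and the article appears to state both.

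**Working it through.** The article gives no UTI rate, no length of stay and no repeat-infection rate, so there is no figure to reproduce. The two calculations below show size under stated assumptions.

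**A. Unequal observation time**

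Inputs:
- POUR incidence 28.1% with tamsulosin and 15% with moxibustion (Sample Size section). The difference is 0.281 − 0.15 = 0.131.
- Assumed: mean stay L = 6 days in the tamsulosin arm, s = 1 to 2 days saved per avoided POUR, and the same constant daily UTI hazard in both arms.

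With hazard h, the risk over a stay of t days is 1 − exp(−h·t), which is close to h·t when small. With equal hazards the risk ratio (moxibustion over tamsulosin) is therefore about the ratio of stays: RR ≈ (L − 0.131·s)/L.

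- s = 1: (6 − 0.131)/6 = 5.869/6 = 0.98
- s = 2: (6 − 0.262)/6 = 5.738/6 = 0.96

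Varying the assumed stay:
- L = 4: 1 − 0.131/4 = 0.97 and 1 − 0.262/4 = 0.93
- L = 8: 1 − 0.131/8 = 0.98 and 1 − 0.262/8 = 0.97

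If the mean stay itself differed by a full day or more, the effect would be larger: 5 v 6 days gives 5/6 = 0.83, and 4 v 6 days gives 4/6 = 0.67. The exact exponential formula at daily hazards of 0.5% to 2% agrees: 6 v 5 days gives 1.19 to 1.20, whose inverse is 0.83 to 0.84. To reach such differences through avoided POUR alone, each avoided case would have to save 1/0.131 = 7.6 days (for 1 day of mean stay) or 2/0.131 = 15.3 days (for 2 days).

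**B. Infections instead of patients**

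Inputs:
- 180 patients per group (Sample Size section) and a two-sided 5% level (Statistical Methods).
- Assumed: 3% to 10% of patients infected, equally in both arms, and a fraction q of infected patients with a second infection.

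The table gives the rejection rate of the uncorrected chi-square test in 100,000 simulated trials per setting with no true difference:

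| Count tested | Rejection rate |
|---|---|
| Patients with UTI | 4.6% to 5.0% |
| Infections, q = 0 | identical to patients |
| Infections, q = 10% | 6.9% to 7.4% |
| Infections, q = 20% | 8.8% to 9.5% |
| Infections, q = 30% | 10.6% to 11.5% |

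A hand check for rare infections: the true variance exceeds the variance assumed by the test by (1 + 3q)/(1 + q). At q = 10% this is 1.3/1.1 = 1.18. The effective critical value is 1.96/√1.18 = 1.80, a two-sided error of about 7%, in line with the simulation.

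**C. The text and Table 1 side by side**

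Item 3 covers the whole stay, while the Table 1 row has one tick that reads as 24 h. Length of hospitalization is ticked in the same way and cannot be known at 24 h, so the column may be a layout convention. The article does not say so.

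**The case against.** Much of the defence is sound.

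- **Pre-operative infections.** A reader might infer that these are counted. The article does not say that. It fails to set a post-operative start, but the Table 1 row is labelled as incidence, which suggests new cases. Exclusion criterion 6 removes urinary system diseases through an open-ended list that could cover a known UTI, although UTI is not named. What remains is an infection arising or found between admission and surgery. It would precede treatment and be balanced by randomisation on average.
- **Numerator.** The words for occurrence and incidence, the denominator of people and the choice of a chi-square test all suggest that a patient-level count is meant. Nothing in the article supports a repeat rate of 10% to 30% within one stay. With no repeats there is no effect.
- **Size of the bias.** A reader might take ratios such as 0.83 or 0.67 as the expected distortion. They need a difference of 1 to 2 days in mean stay, which the POUR route does not produce under plausible savings. The Background also speaks of recovery, not of hospital stay.
- **Constant hazard.** The Background links UTI to POUR and catheterization, and the Interventions section places catheterization within 24 h. If infections cluster early, a shorter tail of observation loses few of them. A UTI may also lengthen the stay, so dependence runs in both directions.
- **Visibility.** Length of stay is compared between arms, so readers would see a difference in observation time.

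These arguments reduce the size of the problem but do not remove it. The article fixes the window, the numerator and the test itself, so this is not a detail left to another document. Surgeons, practitioners and patients are unblinded (Blinding section), so stay could also differ for reasons other than POUR. Seeing a difference in stay does not correct the UTI comparison.

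**Conclusion.** The point holds as a minor defect in one secondary outcome. As written, the UTI rule allows unequal observation time between arms and a count that is not one result per patient, and it does not agree with Table 1.

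The likely distortion from the window is a risk ratio of about 0.96 to 0.98. This rests on an assumed 6-day stay, 1 to 2 days saved per avoided POUR, a constant hazard and the design difference of 13.1 points. It would be larger only if mean stay differed more than that route implies. The numerator has an effect only if some patients have more than one UTI.

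The documents do not support the stronger conclusions that pre-operative infections are counted by design, that a large spurious benefit is to be expected, or that the false-positive rate is materially raised. The primary outcome and the sample size are not affected.

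**What to change.** Reword Secondary Outcomes item 3 along these lines: the number of patients with at least one new UTI between the end of the operation and a fixed post-operative day, the same in both arms, divided by the number of patients in each group; a UTI present before surgery is not counted.

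The trial team should name the day from the department's usual stay, choosing one by which patients are normally still in hospital. The article gives no stay lengths from which to set it here. The chi-square test then fits the outcome. Report UTI over the whole stay descriptively, beside length of stay, and bring the Table 1 row into line with the chosen window.

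Telephone follow-up of patients discharged early is better avoided. It would add self-report from unblinded patients in that subset only, and so a new difference in ascertainment.

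**Cost:** a change of wording, and the date of each UTI must be available from the case report form. The downside is that in-hospital infections after the fixed day leave the tested comparison and appear only in the descriptive result. Treatment, primary outcome and sample size do not change.
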